##### 2.5.4.2.2 Anthropometry and morbidity data

At the time of admission, baseline data on weight, mid upper arm circumference, appetite, illnesses symptoms and signs, rash and growth pattern will be collected. Subsequently, weight will be measured daily before the first meal while the mid upper arm circumference will be measured weekly. The height will be measured once at admission. A 24-h recalls of the presence of the following symptoms will be carried out daily:

- Fever
- Change of mood
- number of stools/ 24 hours (History from the caretakers and observation during presence at the feeding point)
- vomiting : number of time for the previous 24/hours (8:00 to 8:00)
- Complain of abdominal pain
- Abdominal distension
- Rashes
- Cough
- All other observed symptoms will also be recorded.

A qualitative assessment of other food consumed by the child during the 24 hours will also be recorded daily.

##### 2.5.4.2.3 Liking and disliking rating

During each phase, the hedonic scale will be used twice to assess child feeling regarding the RUTF. The first session of assessing the liking or disliking will be done at the beginning of the phase and the second will be done after 7 days of intake. Three methods will be used for ascertaining the rating: facial observation by a trained research officer, showing pictures of the different rating to the child for him to select the appropriate picture and when appropriate by asking the child to verbalise his feeling. Each child will be asked daily to confirm his willingness to continue taking the RUTF.

##### 2.5.4.2.4 Hydrogen breath test

The hydrogen breath tests will be done using the Gastrolzyzer+® to measure carbohydrate malabsorption. The test will be realised the last day of the phase for a sub-sample of children enrolled in the acceptability trial. The day before the test, mother will be advised to not give breakfast to the child and arrive as early as possible on the site. A baseline breath measurement will be taken upon arrival at the CBCC following which each child will receive a sachet of the food of his study arm and phase. Subsequently the hydrogen concentration in the exhaled air will be measured every 15 minutes for first hour and then every 30 minutes for the next three hours. At each interval, the hydrogen concentration will be measured in triplicate.

Carbohydrate malabsorption will be diagnosed if either or both of the following conditions are met: 1)  $\geq 10$  ppm increase in hydrogen production above baseline after one hour or 2) hydrogen production of  $>20$  ppm after one hour [19].

### 2.5.4.3 Efficacy trial

#### 2.5.4.3.1 Treatment approach

RUTF is mostly used for the outpatient management of SAM and children are normally fed with RUTF by their main caregiver at home. However, to ensure that the research team has full control over the daily RUTF intake of study children, **a day care approach** will be used. The use of the day-care approach will eliminate the potential effect of operational constraints such as sharing, or sale of RUTF and inappropriate intake such as mixing RUTF with other foods that dilute energy and micronutrient densities. Although the use of the day-care approach may increase absenteeism, it will help to categorize children into those who strictly adhered to the protocol and those who did not adhere. It will also help to quantify the average daily intake from RUTF at individual level during the whole period of nutrition rehabilitation. An attempt will be made to capture the intake of other foods that children may eat at home in the evening.

#### 2.5.4.3.2 Treatment protocol

Nutrition and medical management of children of both study groups will be similar and will follow the national guidelines for the management of moderate and severe acute malnutrition in children with a slight change in discharge criteria as described in the table 3 below. The only difference of management between the 2 groups will be the type of therapeutic food. Children will be prescribed 200 kcal/kg/day of either SMS-RUTF (intervention group) or P-RUTF (control group). They will be fed this amount in 4 servings at the day care centre between 9 am and 3 pm.

**Table 3. Admission and discharge criteria for 6 to 59 months old children**

|                  |                                                                   |
|------------------|-------------------------------------------------------------------|
| Admission | MUAC < 115mm                                            |
|                  | Bilateral pitting oedema grade + or ++                     |
|                  | WFH Z-score < - 3 (WHO 2006 curves)                     |
| Discharge | Absence of bilateral pitting oedema for 14 successive days |
|                  | MUAC <math>\geq 125</math>mm for 14 successive days        |
|                  | Absence of acute life threatening infection                |

#### 2.5.4.3.3 Bioelectrical Impedance Analysis

The bioelectrical impedance analysis (BIA) measurements using the Bodystat 1500 MDD system (Bodystat Inc, Douglas, United Kingdom). Children will be measured while lying in supine position with arms and legs slightly abducted from the trunk. The measurement will start after 3 to 4 minutes in that position and will be done with electrodes placed at the dorsal surfaces on wrist (between second and third metacarpals) and ankle (between second and third metatarsals) as placing them only 1cm off the imaginary line of wrist and ankle will affect the percentage of FFM and FM substantially. The proximal and distal electrodes will be a minimum of 5 cm apart. The impedance will be measured at two frequencies (50 KHz and 5 KHz) and the ratio of measured impedance at 50 KHz and 5 KHz also called wellness marker (WM) will be calculated. Phase angle (PA) is related to the resistance (opposition offered by the body to the alternating current) and to the reactance (the variation in the phase of the alternating current due to the conductivity capacity of the cells membranes) and expresses both changes in the amount as well as the quality of soft tissue mass (cell membrane permeability and

soft tissue hydration). Thus, PA is an indicator of membrane integrity and water distribution between the intra- and extra-cellular spaces. For this study the PA calculated by the Bodystat 1500 MDD will be used. Well-nourished age and gender matched from the community will serve as control.

#### 2.5.4.3.4 Body composition using the Deuterium dilution technique

Body fat will also be estimated by the deuterium dilution technique (DDT) at admission and 3 month after recovery. The exam will be done in a child well hydrated with empty bladder. A dose of deuterium of 3g (children <10kg) or 6g (children 10 to 20 kg) will be given in the morning after an overnight fasting, Saliva samples will be collected before giving the deuterium dose (baseline sample) and 3 hours (post-dose 1) and 4 hours (post-dose 2) after taking the dose. The saliva sample will be collected using the technique of cotton wool ball. Participants will avoid eating, drinking and physical activity until the final saliva samples have been taken. After collection, the samples will be stored in a cool box until transferred to a freezer where they will be stored frozen (at  $-20^{\circ}\text{C}$ ) until analysis. The enrichment of deuterium in saliva samples will be measured by Fourier Transform Infrared (FTIR) spectrometry at the Kenya Medical Research Institute (KEMRI). Well-nourished age and gender matched from the community will serve as control.

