### **1.5.2.2 Efficacy trial**

Children staying within 1 hour walking distance from feeding points especially established in the community for the study will be enrolled and will be followed up from admission to nutrition recovery using a day care approach. Enrolled children will attend the site daily from 9 am to 3 pm. Children will be offered 200kcal/kg/day of one of the study RUTF. Children will be declared non-recovered if they don't meet the discharge criteria ( $MUAC \geq 12.5$  cm and no oedema) after 3 consecutive months of treatment. Apart from the difference in study therapeutic food, children of all the three study groups will be treated in the same way in accordance with the national guidelines for the treatment of SAM but using the day-care approach as stated above. The day-care approach allows the elimination of several confounding factors such as sharing or poor intake of the therapeutic food at households' level, inappropriate intake of routine medicines and differences in the product acceptance by caregivers that may affect child feeding of the study food. This approach will also allow close monitoring of side effects such as abdominal pain due to iron intake, flatulence (due to unabsorbed sugar), diarrhoea due to lactose intolerance and appetite suppression due to some oligosaccharides. Anthropometric parameters will be measured daily (weight and MUAC) or weekly (height). Clinical conditions will be assessed daily (appetite, oedema, cough, difficulty of breathing, diarrhoea, dehydration, fever, skin eruption, neurological status, anaemia). Embedded sub-studies will allow the assessment of

- haemoglobin (admission and discharge) with an Haemocue device that uses capillary blood collected at finger prick;
- body composition using deuterium dilution technique (at discharge for both those who recovered and those who did not recover);
- body composition using bio-electrical impedance analysis (at admission or when oedema subside, at time of reaching discharge criteria, at discharge and at 3 months follow up) using a Bodystat 1500 MDD device;
- breast milk intake using the dose-to-mother deuterium oxide dilution technique in children still breastfed at admission (two weeks after the start of the treatment);
- stool calprotectin using a quantitative point-of-care chromatographic immunoassay kit for the assessment of intestinal inflammation (admission, 28 days after the start of treatment, at discharge)

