#### Principal secondary hypotheses:

- 1 Weight gain (g/kg/day) during of children aged 6 to 59 months with SAM treated with FSMS-RUTF is not inferior to that of children with SAM of same age treated with MSMS-RUTF nor to that of those treated with P-RUTF with the fixed non-inferiority margin being 1.5g/kg/day (age group 6 to 23 months and 24 to 59 months to be sampled and analysed separately)
- 2 Time to recovery under treatment from admission to recovery of children aged 6 to 59 months with SAM treated with FSMS-RUTF is within the non-inferiority margin of 14 days when compared to children of the same age treated with MSMS-RUTF or to P-RUTF (age group 6 to 23 months and 24 to 59 months to be sampled and analysed separately).
- 3 Height gain during recovery and 3 months after discharge of children aged 6 to 59 months (admission age) with SAM treated with FSMS-RUTF is not inferior to that of children with SAM of the same age treated with MSMS-RUTF nor to that of children treated with P-RUTF given a fixed non-inferiority margin of 0.5 cm (age group 6 to 23 months and 24 to 59 months to be sampled and analysed separately)
- 4 Proportionally to body weight, percentage of body fat mass (BFM) measured at the time of recovery of children treated with FSMS-RUTF will not be higher than the percentage of BFM in children treated with MSMS-RUTF nor higher than the percentage of BFM of those treated with P-RUTF at the fixed margin of inferiority of 6%.
- 5 Tissues electrical properties assessed by Bio-electrical impedance analysis (BIA) will not be impaired in children treated with FSMS-RUTF when compared to that of children treated with MSMS-RUTF or with P-RUTF given a margin of equivalence to be determined by the synthesis methods based on findings of the SMS-RUTF study recently completed in DRC.

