## 2.5.3 Sample size and randomisation

### 2.5.3.1 Sample size

For the acceptability trial, a convenience sample of 20 children per group will be used. For assessing efficacy, the different sample sizes are calculated for a power of 80% and a level of significance of 0.05. The total sample size will be the total of sample required for the SO1 and SO2. For the other SOs, the calculated sample was lower than that required for the total sample for SO1 and SO2 as indicated in table 2 below.

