| SO7                | Mean
Fat free mass (%)                          | Non-inferiority
clinical trial | Standard deviation=1.62
Margin of non-inferiority = 1.07kg
Loss to follow up=5%                            | 35 per arm
Total=105 children
6-59 months |
| SO8                | Mean
Phase Angle                                | Non-inferiority
clinical trial | Standard deviation=0.7
Margin of non-inferiority = 0.2
Loss to follow up=10%                               | 170/arm
Total= 510 children
6-59 months   |
| SO9                | Mean
height gain
3 months after
discharge | Non-inferiority
clinical trial | Standard deviation=0.7
Margin of non-inferiority = 0.5cm
Loss to follow up=10%                             | 180 /arm
Total=540 children
6-23 months   |
| SO10               | Mean
height gain
3 months after
discharge | Non-inferiority
clinical trial | Standard deviation=0.8
Margin of non-inferiority = 0.3 cm
Loss to follow up=10%                            | 100 /arm
Total=300 children
24-59 months  |
| SO11               | Anaemia rate                                       | Non-inferiority                   | Standard deviation=1.3
Non-inferiority margin = 0.5 g/dl
Loss to follow up=10%                             | 100 /arm Total=300
children (both age group) |

The sample size for non-inferiority assessment is calculated using the software “Power” available at [http://www.sealedenvelope.com/power\\_binary\\_noninferior.php](http://www.sealedenvelope.com/power_binary_noninferior.php) for binary endpoint and [http://www.sealedenvelope.com/power\\_continuous\\_noninferior.php](http://www.sealedenvelope.com/power_continuous_noninferior.php) for continuous endpoint. For binary endpoint, the software uses the formula  $n = f(\alpha, \beta) \times [\pi_s \times (100 - \pi_s) + \pi_e \times (100 - \pi_e)] / (\pi_s - \pi_e - d)^2$  where  $\pi_s$  and  $\pi_e$  are the true percent 'success' in the standard and new (experimental) treatment group respectively  $f(\alpha, \beta) = [\Phi^{-1}(\alpha) + \Phi^{-1}(\beta)]^2$  and  $\Phi^{-1}$  is the cumulative distribution function of a standardised normal deviate [94]. For the continuous endpoint, the Calculation is based on the formula:  $n = f(\alpha, \beta) \times 2 \times \sigma^2 / d^2$  where  $\sigma$  is the standard deviation and  $f(\alpha, \beta) = [\Phi^{-1}(\alpha) + \Phi^{-1}(\beta)]^2$  [95].

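### Body fat, height gain and phase angle: the hypotheses, Table 2 and the procedures disagree on time point, variable or margin, and the SO9 sample size does not follow from its own inputs

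*Protocol*

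**What the plan says.** **Body fat.** Principal secondary hypothesis 4 (sections 1.2 and 2.3.2.2) concerns "percentage of body fat mass (BFM) measured at the time of recovery of children treated with FSMS-RUTF", with a margin of 6%. The endpoint list in 2.5.1.2 also places percentage body fat at recovery. The measurement is scheduled in three places:

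- Section 1.5.2.2: deuterium dilution "at discharge for both those who recovered and those who did not recover".
- Section 2.5.4.3.4: "Body fat will also be estimated by the deuterium dilution technique (DDT) at admission and 3 month after recovery".
- Table 4: body fat mass and fat-free mass at admission, week 2 and discharge, with no month-3 entry.

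Table 2, SO7, names fat-free mass in per cent, with SD 1.62 (no unit) and "Margin of non-inferiority = 1.07kg". It prints 35 per arm.

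**Height gain.** Hypothesis 3 applies to both age groups, "given a fixed non-inferiority margin of 0.5 cm". Table 2 uses 0.5 cm for 6–23 months (SO9: SD 0.7, 10% loss, 180 per arm). For 24–59 months (SO10: SD 0.8, 10% loss, 100 per arm) it has "Margin of non-inferiority = 0.3 cm".

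**Phase angle.** Hypothesis 5 has "a margin of equivalence to be determined by the synthesis methods", based on an earlier completed trial. Table 2, SO8, uses SD 0.7 and a fixed non-inferiority margin of 0.2, and prints 170 per arm.

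**The concern.** These are principal secondary hypotheses, and 2.5.1.2 lists their endpoints among the principal ones. Section 2.2 says efficacy should not rest on anthropometry alone, so body composition carries weight in the argument for the product.

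- A team working from 2.5.4.3.4 would not collect body fat at recovery, and a missed recovery measurement cannot be made later.
- SO7 sizes a different variable in a different unit, so it does not show that the 6% body fat comparison is adequately sized.
- In children of 24–59 months, a confidence limit for the height deficit between 0.3 and 0.5 cm passes one stated margin and fails the other.
- For phase angle, the protocol names two kinds of margin (equivalence and non-inferiority) and gives a value for only one of them.
- Section 2.5.3.1 cites Table 2 to show that the other objectives need fewer children than the primary ones. A row whose N does not follow from its inputs weakens that support.

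**Working it through.** **Inputs.** Section 2.5.3.1 says "the different sample sizes are calculated for a power of 80% and a level of significance of 0.05". It does not give the number of sides there. Section 1.5.3.2 uses a one-sided 95% limit for the primary objectives. The formula printed under Table 2 for continuous endpoints is n = f × 2 × SD² / d², with f = (z_α + z_β)². At one-sided 0.05 and 80% power, f = (1.645 + 0.842)² ≈ 6.183. Loss is applied as n / (1 − loss).

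**Rows that reproduce, which fixes the convention**

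- SO8: 6.183 × 2 × 0.49 / 0.04 = 151.5, so 152; 152 / 0.9 gives 169 (printed 170).
- SO10: 6.183 × 2 × 0.64 / 0.09 = 87.9, so 88; 88 / 0.9 gives 98 (printed 100).

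**SO9**

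- 6.183 × 2 × 0.49 / 0.25 = 24.2, so 25; 25 / 0.9 gives 28 per arm, 84 in total (printed 180 and 540).
- Strictest variant, one-sided 0.025 and 90% power: f ≈ 10.51; 10.51 × 2 × 0.49 / 0.25 = 41.2, so 42; 42 / 0.9 gives 47.
- Working backwards from 180 × 0.9 = 162 evaluable: SD = 0.5 × √(162/2) / 2.487 = 1.81 at a 0.5 cm margin, or margin = 0.7 × 2.487 / √(162/2) = 0.19 cm at SD 0.7.

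**SO10 at the hypothesis margin of 0.5 cm**

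- 6.183 × 2 × 0.64 / 0.25 = 31.7, so 32; 32 / 0.9 gives 36. The printed 100 per arm covers either margin.

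**SO7**

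- As printed: 6.183 × 2 × 1.62² / 1.07² = 28.3, so 29; 29 / 0.95 gives 31 (printed 35, which may be upward rounding).
- For percentage body fat the protocol gives no SD. If 6% means 6 absolute points, 35 per arm leaves 35 × 0.95 ≈ 33 evaluable. The largest SD this supports is 6 × √(33/2) / 2.487 ≈ 9.8 points.

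**Deuterium time points side by side**

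| Source | Admission | Week 2 | Recovery/discharge | 3 months after |
|---|---|---|---|---|
| Hypothesis 4, endpoint list | – | – | yes | – |
| 1.5.2.2 | – | – | yes | – |
| 2.5.4.3.4 | yes | – | – | yes |
| Table 4 | yes | yes | yes | – |

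Section 2.5.4.3.4 alone lacks the time point that the endpoint needs. Table 4 is available here only as extracted text and its columns could have shifted, but the conflict between 1.5.2.2, hypothesis 4 and 2.5.4.3.4 does not depend on it.

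**Phase angle.** Section 2.3.3 exempts secondary objectives 8, 15 and 16 from fixed margins. Number 8 is phase angle in Table 2 but breast-milk intake in 2.3.1.2, and hypothesis 8 gives breast milk a fixed margin of 100 g/day. Neither list reaches 15 or 16. The exemption fits phase angle only if Table 2's numbering is meant, and Table 2 still uses 0.2.

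**The case against.** The strongest reply is that little of this alters the trial.

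- **Timing.** Two places already schedule a discharge measurement, so a reader might infer from 2.5.4.3.4 that body fat at recovery will never be measured. The document as a whole does not support that. It supports a contradiction in the procedure section, and Table 4 needs no discharge entry added.
- **SO9.** A reader might infer that a printed input is wrong by a factor of about 2.6 (1.81 / 0.7), or that the trial is wrongly sized. Neither follows. The printed N may be the error: SO6 also prints 30 per arm where the formula gives 8. Section 2.5.3.1 takes the total from SO1 and SO2 (250 and 150 per arm), both above the SO9 and SO10 figures.
- **Height.** Hypothesis 3 calls 0.5 cm fixed, and nothing says that the margin will be picked after the data. This stands, but the protocol still prints two values for the same age group and does not say that 0.3 cm is only for planning.
- **Phase angle.** A working value of 0.2 for sizing can coexist with a margin derived later from an external completed study, and the derivation may sit in an analysis plan not seen here. This is the weakest part. It would be wrong to infer that 0.2 is the correct margin, because the protocol never justifies it as such. What remains is that equivalence and non-inferiority are both named and the two places are not linked.
- **SO7.** The gap between 31 and 35 is not a defect. The mismatch of variable and unit is.

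**Conclusion.** The inconsistencies hold and merit correction. They affect secondary endpoints only, not the primary analysis or total enrolment.

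- **Body fat:** 2.5.4.3.4 omits the time point that hypothesis 4 needs, and SO7 sizes another variable with a kg margin unrelated to 6%. Whether 35 per arm is enough depends on an SD that the protocol does not give; it is enough up to about 9.8 points if 6% is absolute.
- **Height gain, 24–59 months:** two margins, 0.5 and 0.3 cm. The printed sample serves either (36 or 98 needed against 100), so the issue is the decision rule and not the size.
- **SO9:** 28 per arm on the printed inputs, at most 47 under the variants tried, against 180. The protocol does not show which figure is wrong; SD 1.8 or margin 0.19 cm are only values that would fit.
- **Phase angle:** an unspecified equivalence margin and a fixed non-inferiority margin of 0.2 need reconciling, with no presumption about which is right.

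The arithmetic assumes the protocol's formula, a true difference of zero and, unless stated, one-sided 0.05 with 80% power, under which SO8 and SO10 reproduce to within rounding.

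**What to change.** 1. Amend 2.5.4.3.4 so that deuterium dilution includes recovery/discharge, and make the admission, week 2 and 3-month time points agree across 1.5.2.2, 2.5.4.3.4 and Table 4.
2. Restate SO7 for percentage body fat with the hypothesis margin. Say whether 6% means absolute points, and give the SD used with its source.
3. State one height-gain margin per age group, identical in hypothesis 3 and Table 2, before analysis.
4. Correct whichever of SD, margin or N is wrong in SO9.
5. State one phase-angle margin before analysis, say whether the test is non-inferiority or equivalence, and show how the margin was obtained. Align the objective numbers in 2.3.3 with the list they refer to.

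The cost is amendment wording and a few recalculated table cells. Total enrolment does not change on account of SO9 or SO10. The deuterium sub-study would need more than 35 per arm only if the SD of percentage body fat exceeds about 9.8 points at a 6-point margin, so a claim of no extra measurements has to wait for that SD.

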**Principal secondary specific objectives:**

- 1 Compare weight gain of children aged 6-59 months with SAM treated with FSMS-RUTF with that of those treated with MSMS-RUTF and to that of children of same age treated with P-RUTF (age group 6 to 23 months and 24 to 59 months to be sampled and analysed separately)
- 2 Compare time to recovery of children aged 6-59 months with SAM treated with FSMS-RUTF with that of those treated with MSMS-RUTF and to that of children of same age treated with P-RUTF (age group 6 to 23 months and 24 to 59 months to be sampled and analysed separately)
- 3 Compare height gain at 3 months after discharge of SAM children 6 to 59 months treated with FSMS-RUTF or MSMS-RUTF between them and to that of children of same age treated with P-RUTF (age group 6 to 23 months and 24 to 59 months to be sampled and analysed separately)
- 4 Compare deuterium dilution technique estimated body composition (Body Fat Mass, percentage body Fat Free Mass and lean mass) change at full recovery of children treated with FSMS-RUTF, MSMS-RUTF and P-RUTF
- 5 Compare change in phase angle over time of children treated with FSMS-RUTF, MSMS-RUTF, P-RUTF.

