## 2.4 Setting

The research programme will be conducted in the Central Region of Malawi. For the acceptability trial, two CBCCs will be used for the study. We have pre-agreement with several CBCCs but the final choice of the CBCCs will be made in January 2015 based on the functionality and on the number of children attending the centres at that time. The efficacy trial will be carried out in 3 Health District of the Central Region as recommended by the Ministry of Health. These Health Districts are Lilongwe, Dedza and Mchinji. Pre-agreement have been secure with the District Health Officers (DHO) of these Health Districts. In each Health District, a Cluster (a sub-administrative area in Malawi administrative organisation) with the highest burden of acute malnutrition according to the 2014 monthly routine statistics will be selected. In total, 30 community based feeding centres will be established (10 in each District) in the catchment areas of OTP sites that reported more than 60 admissions of SAM cases in 2013. The list will be finalised based on the 2014 statistics and after a field visit has cross-checked the routine statistic figures. The Central region has the worst indicators for undernutrition among under-five children. During the 2010 Malawi Demographic Survey, the prevalence of stunting was 47.2% while that of underweight was 13.5%. The prevalence of wasting is low at 1.8% for severe wasting and 4.3% for wasting. However, this figure underestimates the actual incidence of SAM because up to 80% of cases are oedematous in Malawi and they are not included in these statistics[93]. Indeed, according to

Ministry of Health, by the end of August 25,313 children with SAM had been admitted to CMAM in 2013/2014 consumption year (UNICEF, Malawi situation report, July and August 2014).

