This endpoint will be expressed in person-months and calculated as follow:

$$\text{incidence of deaths} = \frac{\text{n deaths}}{\Sigma \text{ time of observation}}$$

(g) Percentage body fat mass

Percentage of body fat will be calculated by the laboratory performing the analysis. After determining total body water and total lean mass, the total body fat mass will be obtained by subtracting the lean mass to the total body weight. Then percentage body fat will be calculated as follow:

$$\%Body\ Fat\ mass = \frac{\text{Calculated Body Fat Mass(kg)} * 100}{\text{Body weight(kg)}}$$

(h) Phase angle

The phase angle will be provided by the BIA device.

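### The deuterium schedule is stated three ways, and an admission baseline with no oedema rule distorts the change in body composition that objective 4 compares

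*Protocol*

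**What the plan says.** Protocol section 2.5.4.3.4 sets the deuterium timing: "Body fat will also be estimated by the deuterium dilution technique (DDT) at admission and 3 month after recovery". Its only condition on the child's fluid state is "The exam will be done in a child well hydrated with empty bladder". The sub-study list in section 1.5.2.2 instead places deuterium at discharge, for recovered and non-recovered children alike. Table 4 (section 2.5.4.4) marks body fat mass and fat free mass at admission, week 2 and discharge, without naming a method.

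Section 2.5.1.2(g) gives the derivation. It starts "After determining total body water and total lean mass", and then "the total body fat mass will be obtained by subtracting the lean mass to the total body weight". The laboratory does the calculation, and no hydration factor is stated.

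Principal secondary objective 4 (section 2.3.1.2) begins "Compare deuterium dilution technique estimated body composition" and concerns its change at full recovery. Hypothesis 4 (section 2.3.2.2) is different: it concerns percentage body fat measured at recovery, with a 6% margin.

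Impedance has an oedema rule: "body composition using bio-electrical impedance analysis (at admission or when oedema subside, at time of reaching discharge criteria". Deuterium has none. Section 2.5.2.2 admits oedema of any grade, section 2.4 says that "up to 80% of cases are oedematous in Malawi", and Table 3 requires 14 oedema-free days for discharge.

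**The concern.** A change needs two comparable measurements. If the first is taken with oedema present and the second after it has cleared, the difference contains loss of oedema water as well as change in tissue. Deuterium measures total body water and cannot by itself tell oedema water from water in lean tissue. The step from body water to lean mass therefore credits oedema to lean tissue, and fat, obtained by subtraction, comes out too low.

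Every food would then appear to deposit more fat and rebuild less lean tissue than it does, by an amount that varies with each child's oedema. Timing has to be settled before the sub-study starts, because a baseline measured with oedema present cannot be retaken. The protocol already allows for this with impedance, so the omission for deuterium looks unintended.

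**Working it through.** **1. The schedules side by side**

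| Place | Admission | Week 2 | Discharge or recovery | 3 months after |
|---|---|---|---|---|
| Section 1.5.2.2 | no | no | yes | no |
| Section 2.5.4.3.4 | yes | no | no | yes |
| Table 4 (method not named) | yes | yes | yes | no |

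On section 1.5.2.2 there is no baseline, so objective 4 cannot be computed. On section 2.5.4.3.4 there is a baseline but no recovery measurement. Only Table 4 supplies both, provided its rows mean deuterium. The oedema problem arises on the second and third rows and not on the first.

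**2. Direction**

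Let E be oedema water and h the water fraction of lean tissue. Estimated lean mass is total body water divided by h, and fat is weight minus lean mass. Oedema adds E to weight and E to body water, so:

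- estimated lean mass rises by E/h;
- estimated fat mass falls by E(1/h − 1), which is positive for any h below 1.

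The direction therefore does not depend on the numbers assumed.

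**3. Size**

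The plan states no figure for this effect to reproduce. The inputs are assumptions that the documents do not give: h of 0.75 to 0.80, fat equal to 12% of oedema-free weight, and oedema water a share o of admission weight. Then

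estimated fat share = 1 − 0.88(1 − o) − o/h = 0.12 − o(1/h − 0.88).

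Shortfall against the oedema-free 12% is o(1/h − 0.88). This splits into o(1/h − 1), from scoring water as lean, and 0.12·o, from the heavier denominator.

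| o | Total shortfall (h 0.80 to 0.75) | Water scored as lean | Denominator |
|---|---|---|---|
| 5% | 1.9 to 2.3 points | 1.3 to 1.7 | 0.6 |
| 10% | 3.7 to 4.5 | 2.5 to 3.3 | 1.2 |
| 15% | 5.6 to 6.8 | 3.8 to 5.0 | 1.8 |

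In kilograms, take an 8 kg child with o = 10% and h = 0.79. E is 0.8 kg, true fat is 0.12 × 7.2 = 0.864 kg and true lean mass is 6.336 kg. Body water is 0.79 × 6.336 + 0.8 = 5.805 kg, so estimated lean mass is 5.805/0.79 = 7.349 kg, about 1.0 kg too high. Estimated fat is 8 − 7.349 = 0.651 kg, or 8.1%, about 0.21 kg too low.

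A wider set of assumptions (oedema 2 to 15% of oedema-free weight, fat 5 to 15%, same h) gives a shortfall of 0.6 to 6.3 points. Slight oedema matters little.

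**4. Between arms**

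Allocation is random, so the expected oedema share is the same in each arm and the expected bias in the arm difference is zero. What remains is chance imbalance. Section 2.5.3.2 separates the randomisation lists by age only. With the 35 per arm that Table 2 gives for fat free mass, and 80% of children oedematous, the standard deviation of the difference in oedematous share is √(2 × 0.8 × 0.2/35) = 0.096. If all oedematous children carried the same oedema share, the arm difference in change would shift by chance with a standard deviation of 0.096 × 1.9 ≈ 0.2 to 0.096 × 6.8 ≈ 0.65 points. Differences in oedema between children add further variance within arms.

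**The case against.** The strongest reply is that the problem is conditional. If the discharge-only schedule of section 1.5.2.2 governs, no deuterium baseline exists and nothing is contaminated. Table 4 names no method, and impedance can also yield fat and fat free mass. This stands: the defect on the face of the document is the conflict of schedules, and the oedema point follows from an admission baseline. But it does not clear the plan, because the discharge-only schedule leaves objective 4 without a change to compare.

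A reader might infer that the body-fat hypothesis test is biased, or that an error of up to 7 points uses up the 6% margin. The documents do not support this. Hypothesis 4 and the endpoint list in section 2.5.1.2 use percentage fat at recovery, when children are oedema-free. The margin is a between-arm limit for that measurement and is no yardstick for a within-child error at admission. A reader might also infer that the excess-fat question of section 2.1 would be answered wrongly. The earlier DRC trial judged it against community controls, and Table 4 places the controls' body fat under discharge, so that comparison does not use the admission value.

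Oedema is not ignored in the analysis. Section 1.5.4.2 plans subgroups by type of malnutrition, and section 2.5.6.2.1 checks interactions with the form of SAM. These help in reading the results but do not remove the artefact from the oedematous subgroup.

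The size is also open to challenge. The 80% in section 2.4 describes cases in Malawi and does not forecast this sub-study. Complicated cases enter only after stabilisation, and Table 3 lists only the two lower oedema grades where section 2.5.2.2 says any grade. Nothing in the documents supports oedema of 10 to 15% of weight in particular. All of this stands, and it is why the size is given as a range under assumptions.

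**Conclusion.** The concern holds in a limited form. The three deuterium schedules cannot all apply, and neither of the two that name deuterium supports the change in objective 4. Where the baseline is taken at admission, as section 2.5.4.3.4 states, fat is understated and lean mass overstated in oedematous children. Within-arm fat gain to recovery is then overstated and lean gain understated. The direction is certain for any hydration factor below 1.

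The size rests on assumed hydration, fat and oedema shares: about 2 to 7 points of percentage fat per oedematous child, of which about 1.3 to 5.0 points are water scored as lean. The arm comparison of change has no expected bias and suffers only added noise and chance imbalance. Percentage fat at recovery and the comparison with community controls are sound on this point.

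**What to change.** Reconcile sections 1.5.2.2 and 2.5.4.3.4 and Table 4 to one deuterium schedule that includes a baseline and a measurement at recovery, and name the method in Table 4's body fat and fat free mass rows. Time the baseline by the protocol's own impedance rule, "body composition using bio-electrical impedance analysis (at admission or when oedema subside", and use the weight taken on that day. Adjust the arm comparison of change for oedema at admission.

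The cost is mainly protocol wording, with some baseline tests moved to a later day. The downside is that oedematous children get a baseline some days into treatment, at a time that differs between children and that the allocated food could influence. The protocol already accepts a delayed baseline for impedance.

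Oedematous children should not be excluded from the change analysis. If 80% of 35 per arm were oedematous, only about 0.2 × 35 = 7 per arm would remain.
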